### Allocation

3.9

Participants will be required to fill out eligibility and baseline questionnaires accessible through the Internet in addition to completing an interview. Only qualified individuals who provided consent will be randomly assigned to the experimental or control group. Participants will then be informed regarding the allocation results to increase study transparency. The random assignment will be performed by the Central Registration Center located at Kurashiki Heisei Hospital, Okayama Prefecture. The randomized list will be generated using an Excel spreadsheet by a third party not involved in this study and will be provided to the Central Registration Center. The randomized list will be created using a reasonably sized permuted block method, the block size of which will not be disclosed until the end of this trial to ensure concealment.

### Blinding

3.10

Considering the unique nature of the intervention, participants and therapists cannot be blinded. Therefore, this trial will employ an Internet questionnaire to blind the assessors.

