### Trial design

2.1

This 5-week, single-blind, 2-arm, parallel-group, randomized, pilot RCT will determine the effectiveness of with the SPSRS application by comparing individuals who had and had not been exposed to the same.

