#### Control group

3.2.2

The control group will receive no intervention and no instruction to watch videos using the SPSRS application or other video playback applications during the 5-week intervention period.

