### Outcomes

3.5

The primary outcome will include changes in the CES-D score^[28]^ after the 5-week intervention, while the secondary outcome will include changes in the Kessler Screening Scale for psychological distress (K6)^[31]^ and the generalized anxiety disorder 7-item scale (GAD-7)^[32]^ score following the 5-week intervention.

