#### Center for epidemiologic studies depression scale

3.11.2

The CES-D is a 20-item self-reported questionnaire that measures depressive symptoms using 4 subscales related to “somatic and retarded activity,” “depressed affect,” “positive affect,” and “interpersonal problems.”^[28]^ The CES-D uses a 4-point Likert scale (A = <1 day, B = 1–2 days, C = 3–4 days, and D = 5–7 days), with each item being scored 0 to 3, respectively. Participants may have a total score of 0 to 60 points, with a higher score indicating stronger depressive symptoms. The reliability and validity of CES-D have already been verified.^[28,37,38]^

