### Access to data

3.20

Prior to the publication of major results, only data managers and principal investigators will have access to the complete dataset. Data managers and principal investigators will address problems related to the data and finalize a dataset for statistical analysis. After publication, only the principal investigator and individuals approved by the principal investigator will have access to the dataset.

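### The trial is labelled single-blind with blinded assessors, but all three outcomes are self-rated by participants who know their arm, so none is assessed blind

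*Protocol article*

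**What the plan says.** The Abstract (Methods) and section 2.1 Trial design both give the trial a single-blind label; section 2.1 begins "This 5-week, single-blind, 2-arm, parallel-group, randomized, pilot RCT".

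Section 3.10 Blinding states that "participants and therapists cannot be blinded" and follows directly with "Therefore, this trial will employ an Internet questionnaire to blind the assessors". It names no other blinded role.

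Section 3.5 Outcomes begins "The primary outcome will include changes in the CES-D score" and lists the K6 and GAD-7 as secondary. Section 3.11.2 says "The CES-D is a 20-item self-reported questionnaire", and sections 3.11.3 and 3.11.4 describe the K6 and GAD-7 as self-report too. Section 3.12 says that outcomes are collected by an Internet questionnaire.

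On knowledge of the arm, section 3.9 Allocation says: "Participants will then be informed regarding the allocation results to increase study transparency". Section 3.2.2 describes the comparator: "The control group will receive no intervention and no instruction to watch videos".

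The limitations paragraph of section 4 Discussion accepts that participant and therapist bias may be present. It offers concealed hypotheses and standardized guidance and feedback as mitigation, and it advises care in interpretation.

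**The concern.** Assessor blinding protects an outcome when someone other than the participant makes the rating and that person does not know the arm. With a self-report scale the participant makes the rating, so there is no separate assessor to blind. Section 3.10 therefore claims a safeguard that its own method cannot supply for any outcome named in section 3.5.

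Two uses of the results depend on this. First, section 2.1 says that the trial will determine effectiveness, and section 4 says that the pilot can provide evidence supporting use of the application in practice. How far a reader trusts a subjective between-group difference depends on whether it was rated blind. Second, sections 3.7 and 4 say that the results will feed the sample size of the full-scale trial, and section 3.7 names the between-group difference and the SD. If part of the observed CES-D difference comes from knowing one's arm, the planning effect is too large and the full-scale trial too small for the effect of the application itself.

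The contrast gives room for such an effect. Under section 3.3 the experimental arm receives daily messages encouraging use and weekly messages on viewing time. The control arm receives nothing during the five weeks.

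**Working it through.** No arithmetic beyond a count applies, and the article gives no figure to reproduce. The check is to list each named outcome, who rates it, and whether that person knows the allocation.

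| Outcome (3.5) | Role | Rater | Source | Rater knows the arm? |
|---|---|---|---|---|
| CES-D | primary | participant | 3.11.2 | yes (3.9, 3.10, 3.2.2) |
| K6 | secondary | participant | 3.11.3 | yes (same) |
| GAD-7 | secondary | participant | 3.11.4 | yes (same) |

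Outcomes named: 3. Rated by a participant who knows the arm: 3. Rated by a blinded assessor: 3 − 3 = 0.

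**Do participants really know their arm?** Yes, on three independent grounds. Section 3.9 says that they are told, section 3.10 says that they cannot be blinded, and section 3.2.2 gives the controls nothing that could be mistaken for the application.

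**Is any outcome rated by someone else?** The only interview instrument described is the MINI. Its stated use, in section 3.1, is to exclude people with a recent major depressive episode, and section 3.5 does not list it as an outcome. The content of Table 1 (the assessment schedule) is not available here, so a MINI after randomization cannot be fully ruled out, but no text names one as an outcome. Under section 3.16 the investigator evaluates adverse events; these are not a named outcome, and no blinding is stated for them.

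**What does the Internet questionnaire achieve?** It keeps staff out of the room when the participant answers, so a therapist or researcher cannot steer the response at that moment. It leaves the respondent's own knowledge and expectations untouched.

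**Does the Discussion repair the statement?** It acknowledges that bias may be present. It does not withdraw the single-blind label, and it does not say that the unblinded participant is the outcome rater. Concealing the hypotheses is a partial measure at best. Section 3.18 has potential risks and benefits explained before consent, section 3.3 sends encouragement to one arm only, and section 3.12 lets controls have the application after week 5. A participant could readily guess which arm is expected to improve.

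**The case against.** The strongest reply is that the article is open about the main fact. Section 3.10 says outright that participants and therapists are unblinded, and the Discussion repeats the difficulty, names mitigations and urges caution. The stated objective in section 2 is feasibility, in 32 people. On this view the fault is loose wording, and a reader who takes sections 3.10 and 4 together would not be misled. Much of this stands. The article does not hide that participants are unblinded, and online self-completion is a limited but real protection against one route of bias. What does not follow is that the label is correct: a disclosed limitation and a claimed safeguard still sit side by side, and the claim is wrong for all three outcomes.

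The following stronger readings are not supported:

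- **That the trial has no protection at all, or that expectancy enters the score undiminished.** The online form removes interviewer influence, and the concealed hypotheses may have some effect. All that can be said is that no blinding of the rater limits expectancy effects.
- **That the bias can be expressed as a share of the treatment effect.** The article gives neither an expectancy effect nor an expected treatment effect, so any such ratio would divide one assumption by another.
- **That the data handlers are unmasked.** Section 3.20 says "Data managers and principal investigators will address problems related to the data and finalize a dataset for statistical analysis" without mentioning masking, but that is silence, and an article may leave the matter to the full protocol or analysis plan. Sections 3.13 and 3.19 also describe separate binders for evaluation and intervention forms and survey materials identified by participant number. These do not establish masking, but they do not contradict it.
- **That the registry entry is wrong.** It has not been seen.
- **That the article wrongly credits the displayed words with any difference.** That question concerns the choice of comparator. Section 2 states the comparison plainly as the application intervention against no intervention.

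**Conclusion.** The point holds as an error in the stated blinding. The trial is labelled single-blind on the strength of assessor blinding, yet 0 of 3 named outcomes are rated by anyone blind to allocation. For its outcomes the trial is effectively open-label.

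This rests on the article's own text for the outcomes, the raters and the disclosure of allocation. It assumes only that the unseen Table 1 adds no blinded, observer-rated outcome. The direction of concern is that expectancy could inflate the self-rated CES-D difference; its size cannot be derived from the document.

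Severity is moderate. The design may be quite reasonable for a pilot, and the Discussion discloses part of the problem. The correction still matters, because it changes what the primary comparison can claim and how the full-scale planners should read it.

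**What to change.** In the Abstract (Methods), section 2.1 and section 3.10, replace the single-blind label and the assessor-blinding claim with a description such as: *open-label with participant-reported outcomes, self-completed online to avoid interviewer influence*. Alternatively, if some role is in fact masked, name it, for example an analyst working with coded arms, and state that the outcome raters are not blinded.

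In sections 3.7 and 4, add that the between-group CES-D difference may include expectancy effects and that this must be allowed for when the pilot estimate is used to size the full-scale trial.

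The cost is a few sentences and a less favourable design label. Recruitment, allocation, outcomes, model and sample size are unchanged. The correction should be made before the results are reported.

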### Data collection

3.11

Before the intervention begins, participants in the experimental group will be provided with a standardized SPSRS application manual and will be trained on how to operate the SPSRS application. To ensure data accuracy and reliability, researchers will undergo training sessions on data collection and storage. In addition, regular meetings will be held to address issues related to trial implementation. Outcome evaluation will follow the schedule outlined in Table 1. Demographic data, such as age, sex, sleep time, smoking habits, exercise habits, and drinking habits, will then be collected as part of the baseline assessment.

#### Mini-international neuropsychiatric interview

3.11.1

The mini-international neuropsychiatric interview (MINI) is structured based on Diagnostic and Statistical Manual of Mental Disorders, 4th Edition and International statistical classification of diseases and related health problems, 10th revision.^[29]^ The present study will be using the Japanese version of the latest MINI (5.0.0), which contains 16 modules for psychiatric diagnosis (major depressive episodes, dysthymia, suicide risk, manic and hypomanic episodes, panic disorders, agoraphobia, social phobia, obsessive–compulsive disorder, posttraumatic stress disorder, alcohol use disorder, substance use disorder, psychotic disorder, anorexia nervosa, bulimia nervosa, generalized anxiety disorder, and antisocial personality disorder), to which respondents may answer with only “Yes” or “No.” The reliability and validity of the Japanese version of the MINI have already been confirmed.^[29]^

#### Center for epidemiologic studies depression scale

3.11.2

The CES-D is a 20-item self-reported questionnaire that measures depressive symptoms using 4 subscales related to “somatic and retarded activity,” “depressed affect,” “positive affect,” and “interpersonal problems.”^[28]^ The CES-D uses a 4-point Likert scale (A = <1 day, B = 1–2 days, C = 3–4 days, and D = 5–7 days), with each item being scored 0 to 3, respectively. Participants may have a total score of 0 to 60 points, with a higher score indicating stronger depressive symptoms. The reliability and validity of CES-D have already been verified.^[28,37,38]^

#### Kessler screening scale for psychological distress

3.11.3

The K6 is a 6-item self-report questionnaire that measures psychological distress using 4 questions about depression and 2 about anxiety.^[31]^ The K6 uses a 5-point Likert scale (4 = all of the time, 3 = most of the time, 2 = some of the time, 1 = a little of the time, and 0 = none of the time). Participants may have a total score of 0 to 24 points, with a higher score indicating stronger psychological distress. The reliability and validity of K6 have already been verified.^[31,39–43]^

#### The generalized anxiety disorder 7-item scale

3.11.4

The GAD-7 is a 7-item self-report questionnaire that measures generalized anxiety disorder using a 4-point Likert scale (0 = not at all sure, 1 = several days, 2 = over half the days, 3 = nearly every day).^[32]^ Participants may have a total score of 0 to 21 points with a higher score indicating stronger anxiety symptoms. The reliability and validity of GAD-7 have already been verified.^[32,44–47]^

### Promoting participant retention and completion of follow-up

3.12

Participants will be informed that the use of the SPSRS application and outcome measurements will be free of cost and that the SPSRS application will allow them to freely select videos to watch so that they can enjoy the intervention. In addition, participants will be provided a dedicated email address through which they may raises their concerns regarding the use of the SPSRS application. Moreover and if necessary, participants in the control group can receive video viewing interventions using the same SPSRS application after measuring outcomes 5 weeks following the start of the intervention. Outcome measurements will be conducted through an easy-to-use Internet questionnaire for the participant's convenience. Participants who satisfy the criteria for refusal or discontinuation of intervention will be asked to participate and provide data for the week 5 assessment. The aforementioned requests and responses will be explained to participants upon obtaining informed consent. No financial or physical incentives will be provided to participants at any point during the evaluation or intervention.

### Data management

3.13

Data will be managed in accordance with methods used in previous studies.^[48–50]^ Accordingly, first and second stage management will be implemented to ensure data accuracy. First stage management will require 2 independent researchers to enter data into an Excel spreadsheet using a computer not connected to the Internet. The input data will then be saved onto a password-protected Universal Serial Bus. Second stage management will require 2 different researchers not involved in the first stage to confirm and double-checked for any potential errors in the input contents. Only individuals authorized by the principal investigator will be allowed access to the database. The Internet questionnaire data of each participant will be printed on paper and deleted after data entry. Paper materials related to each participant's evaluation will be stored in an evaluation binder, while intervention materials will be stored in a separate intervention binder. Binders that store evaluation and intervention forms will be kept inside a lockable shelf at Kibi International University. Paper files will be stored for up to 5 years after the examination ends.

### Statistical methods

3.14

Intention-to-treat analysis will be employed herein using data obtained from all assigned participants. A linear mixed models with the restricted maximum likelihood estimation method will then be used to address values missing from the clinical trial, estimate the mean of the primary and secondary outcomes, and compare the experimental and control groups.^[51]^ Group assignment, evaluation time, and interactions between group assignment and evaluation time will be considered fixed effect factors, while participants will be considered random effect factors. The model will use a fixed effect type III test. A 2-sided *P* value of <.05 will be used to indicate statistical significance. No plans for subgroup analysis are currently in place. The latest version of SPSS (SPSS Japan Inc., Tokyo, Japan) will be used for data analysis. In addition, the effect size (Hedge *g*) between the 2 groups and its 95% confidence interval will also be reported.^[52,53]^

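### The primary mixed model does not adjust for baseline CES-D: its group-by-time test is valid but less precise than a baseline-adjusted week-5 comparison, by an amount that may be small in this trial

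*Protocol article*

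**What the plan says.** Section 3.5 (Outcomes) defines the endpoint as a change: "The primary outcome will include changes in the CES-D score" after the 5-week intervention. K6 and GAD-7 changes are secondary.

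Section 3.14 (Statistical methods) specifies a linear mixed model fitted by REML. Its fixed part is "Group assignment, evaluation time, and interactions between group assignment and evaluation time will be considered fixed effect factors". The random part is a participant effect. For inference, the section says: "The model will use a fixed effect type III test". A two-sided P value below .05 "will be used to indicate statistical significance". The analysis set is everyone randomised: "Intention-to-treat analysis will be employed herein using data obtained from all assigned participants". The same model is meant to deal with missing values.

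On timing, section 3.9 (Allocation) places the baseline questionnaires before assignment: "Participants will be required to fill out eligibility and baseline questionnaires accessible through the Internet in addition to completing an interview". The only later outcome assessment named in the text is week 5; under section 3.12, participants who stop early "will be asked to participate and provide data for the week 5 assessment".

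**The concern.** With one post-baseline assessment, a time factor, a group-by-time term and a participant effect can be estimated together only if baseline is a level of time. Baseline CES-D then enters as an outcome, and the model lets the two arms have different baseline means. Randomisation makes those means equal in expectation, so the model estimates a difference that is known to be zero on average and subtracts it in full. Whenever the regression slope of week 5 on baseline is below 1, full subtraction over-corrects a chance imbalance and adds noise.

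The stake is precision, not validity. There are 16 participants per arm, and section 3.7 says that the between-group difference and SD from this pilot will size the full-scale trial. A more precise difference is available from data that are collected anyway.

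**Working it through.** **Inputs from the article.** 16 per arm (3.7); two-sided 5% level and model terms (3.14); entry at CES-D of 16 or more (3.1); baseline (3.9) and week 5 (3.12) as the occasions. **Assumed**, because 3.7 says the difference and SD are unknown: correlation r = 0.3, 0.5, 0.7; for the CES-D scale, source mean 14, SD 9 and effect 6 points. There is no power figure to reproduce: 32 is 2 × 16, taken from a rule of 15 to 20 per group.

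**Step 1: what the model's terms estimate.** On one simulated complete data set (16 per arm, r = 0.5), the REML random-intercept fit gave a group-by-time coefficient of −6.913, t = −3.205. A two-sample t-test on change scores gave the same estimate and t (p = 0.003). The group main effect was −3.657, t = −1.523, matching a t-test on each person's average of baseline and week 5. With two occasions that average carries (0 + δ)/2 = δ/2.

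**Step 2: equal variances at baseline and week 5.** In units of σ² × 2/n:
- change score: 2(1 − r)
- baseline-adjusted: (1 − r²) × [1 + 1/(2n − 4)], where the bracket is 29/28 at n = 16 and allows for estimating the slope
- ratio: (1 + r)/2 × 29/28

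This gives 0.65 × 29/28 = 0.673, 0.75 × 29/28 = 0.777 and 0.85 × 29/28 = 0.880. Simulation gave 0.67, 0.78 and 0.87. The reductions are therefore about 33%, 22% and 12 to 13%.

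**Step 3: baseline cut at 16.** The cut lies (16 − 14)/9 = 0.222 SD above the assumed source mean. With a = 0.222 and λ = φ(a)/[1 − Φ(a)] = 0.9445, the truncated-normal variance factor is 1 + aλ − λ² = 0.318. Baseline variance is then 81 × 0.318 = 25.74 (SD 5.07). Taking r as the source-population correlation, the slope of week 5 on baseline stays r and the residual variance is 81(1 − r²). The change-score variance is (1 − r)² × 25.74 + 81(1 − r²).

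| r | change variance | residual variance | ratio × 29/28 | reduction |
|---|---|---|---|---|
| 0.3 | 12.61 + 73.71 = 86.32 | 73.71 | 0.884 | 12% |
| 0.5 | 6.43 + 60.75 = 67.18 | 60.75 | 0.937 | 6% |
| 0.7 | 2.32 + 41.31 = 43.63 | 41.31 | 0.981 | 2% |

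Simulation gave ratios of 0.89, 0.94 and 0.98.

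**Step 4: power for a 6-point effect (simulated, SD 9).**

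| r | no restriction: change → adjusted | cut at 16: change → adjusted |
|---|---|---|
| 0.3 | 0.34 → 0.47 | 0.44 → 0.48 |
| 0.5 | 0.46 → 0.56 | 0.52 → 0.54 |
| 0.7 | 0.65 → 0.70 | 0.69 → 0.70 |

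**Step 5: validity.** With no true effect, rejection rates were 0.048 to 0.055 for the group, interaction and adjusted tests. With a true effect of 6, the interaction and adjusted estimates both averaged about 6; the group main effect averaged about 3.

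**The case against.** The strongest reply is that nothing here is wrong. The outcome is change, the model contains group-by-time, and that term is the between-group difference in change. It holds its type I error and is unbiased. This stands: residual chance imbalance in the estimate is sampling variance, not bias.

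A second reply is that the larger gains assume equal variances, while the entry rule narrows the baseline range. This also stands: Steps 3 and 4 show a much smaller gain, so the equal-variance figures are the upper end.

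A third is that this is a pilot with a feasibility objective, for which a few points of power decide nothing. That limits the weight of the point. It does not remove it, because the estimates are to be reused for planning and the improvement needs no new data.

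A reader might also infer that the plan will report half the treatment effect, through the type III group line. The document does not support that. It never names the group main effect as the primary comparison, and the change outcome points to the interaction. A contrast left unnamed in a condensed article may be fixed in an analysis plan that is not shown, so that silence is not counted as a fault. The group line matters only as something not to report as the treatment effect.

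Finally, plain ANCOVA would drop participants without a week-5 score unless values were imputed, against the stated intention-to-treat set. The remedy must respect that.

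**Conclusion.** The point holds as a matter of efficiency. The model as listed makes no use of baseline CES-D as a predictor, and an adjusted comparison would be more precise over the correlations examined. The gain lies between about 33%, 22% and 12 to 13% of the variance (equal variances) and about 11 to 12%, 6% and 2% (baseline restricted by the entry rule), at r = 0.3, 0.5 and 0.7. In the restricted case this is roughly 0 to 5 points of power. The advantage vanishes with equal variances only at a correlation of about 0.93 or more.

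This rests on assumed r, SD, source mean and effect, and on baseline and week 5 being the only occasions. Exact equality with a change-score test also needs complete data; with dropout the planned model additionally uses the baselines of incomplete cases. With k post-baseline visits and a constant effect, the group main effect would carry k/(k + 1) of it rather than half. The change is worth making because it is cheap, not because the planned test misleads.

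**What to change.** In section 3.14, state the primary analysis as the week-5 difference between arms in CES-D, adjusted for baseline CES-D. Estimate it with a constrained longitudinal REML model: baseline and week 5 as outcomes, a common baseline mean for both arms, a time term, a group-by-week-5 term, and an unstructured covariance. The unstructured covariance matters because a random intercept alone forces equal variances at the two occasions, which the entry threshold makes doubtful. This form keeps every assigned participant and the planned handling of missing values.

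Report that single contrast with its 95% CI as the treatment effect, and do not present the type III group main effect as such. Use the same model for K6 and GAD-7.

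The cost is one paragraph of wording and about one degree of freedom. No new data are needed.

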### Eligibility criteria

3.1

Participants will be selected according to the following eligibility criteria:

Inclusion criteria:

(1)Men and women(2)18 years and older(3)Center for epidemiologic studies depression scale (CES-D) score ≥16.^[28]^(4)Owns a smartphone with an iOS operating system.(5)Written informed consent prior to participation.

Exclusion criteria:

(1)Lifetime history of psychiatric disorders.(2)Currently receiving treatment for a mental health problem from a mental health professional.(3)Vision or hearing deficits that negatively impact everyday life.(4)Experience of a major depressive episode 2 weeks prior to the study ascertained using the Mini-International Neuropsychiatric Interview (MINI).^[29]^

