### Sample size

3.7

Four factors are required to calculate the sample size: significance level, power, difference between groups, and standard deviation (SD).^[35]^ However, considering that no previous 2-arm trial has used the SPSRS application for individuals with StD, values for the difference between groups and SD remain unknown. Although a pilot RCT does not require sample size calculations using the aforementioned 4 factors,^[26]^ 15 to 20 participants per group are required to ensure scientific validity of the pilot study results.^[36]^ Therefore, the present study will include a total of 32 participants with 16 participants per group. In addition, the results of this pilot study will provide information on the difference between groups and SD necessary for sample size calculation during the future full-scale study.

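### As written, the mixed model gives CES-D one variance at baseline and week 5; an unstructured 2 x 2 covariance would protect the week-5 intervals and the handling of missing scores at almost no cost

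*Protocol article*

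**What the plan says.** Section 3.14 (Statistical methods) describes the model in two parts. For the fixed part: "Group assignment, evaluation time, and interactions between group assignment and evaluation time will be considered fixed effect factors". For the random part: "participants will be considered random effect factors". Estimation is by REML. No residual covariance structure is named, and no variance specific to an assessment time. The model is meant to "address values missing from the clinical trial, estimate the mean of the primary and secondary outcomes, and compare the experimental and control groups". Hedges g with a 95% confidence interval is also promised, without saying which SD it uses.

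Three other sections bear on this. Section 3.1 admits participants with "Center for epidemiologic studies depression scale (CES-D) score ≥16". Section 3.5 defines the primary outcome as change: "The primary outcome will include changes in the CES-D score". Section 3.7 says that "the results of this pilot study will provide information on the difference between groups and SD necessary for sample size calculation" in the later full-scale trial. It plans 16 participants per group and says that the SD is not known.

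**The concern.** A participant effect plus a constant residual gives every CES-D score the same total variance, whenever it is taken. The entry rule makes that doubtful here. Scores below 16 are excluded at entry, but at week 5 the full 0 to 60 range is open again. If the eligibility score is also the baseline score, baseline spread is cut and week-5 spread is cut much less.

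A pooled variance is then too large for baseline and too small for week 5. Two things are at stake. Model-based intervals for the week-5 means and the week-5 group difference would be too narrow. And when week-5 scores are missing, the model would use the wrong slope of week 5 on baseline to allow for them. A third matter depends on a choice that the article leaves open: if the SD for Hedges g or for the full-scale trial were taken from the pooled model variance, it would be too small for week-5 scores.

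**Working it through.** **Inputs.** From the article: 16 per group (section 3.7), entry at CES-D of 16 or more (3.1), the model terms (3.14). The article gives no SD, so there is no variance figure of its own to reproduce. Assumed: a normal source population with CES-D SD 9, baseline to week-5 correlation 0.6 and mean 12, 16 or 20; two assessments; the eligibility score used as baseline.

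**Step 1, baseline variance.** With a = (16 − mean)/9 and λ = φ(a)/(1 − Φ(a)), the truncated variance is V0 = 81 × (1 + aλ − λ²). For mean 16, a = 0 and λ = 0.798, so V0 = 81 × (1 − 0.637) = 29.4.

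**Step 2, week-5 variance.** V5 = 0.6² × V0 + (1 − 0.6²) × 81. For mean 16: 0.36 × 29.4 + 51.84 = 62.4.

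**Step 3, model variance.** With complete data the REML total variance under a random participant effect and constant residual is (V0 + V5)/2. For mean 16: (29.4 + 62.4)/2 = 45.9.

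**Step 4, week-5 intervals.** The ratio of the model standard error to the true one is the model SD over the week-5 SD. Coverage is approximately 2Φ(1.96 × ratio) − 1.

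| Source mean | Baseline SD | Week-5 SD | Model SD | SE ratio | Approx. coverage |
|---|---|---|---|---|---|
| 12 | 4.7 | 7.7 | 6.4 | 0.83 | 90% |
| 16 | 5.4 | 7.9 | 6.8 | 0.86 | 91% |
| 20 | 6.2 | 8.1 | 7.2 | 0.89 | 92% |

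Simulation at 16 per group (6,000 trials per row) gave coverage of 89.8%, 90.9% and 91.8%, against 94.9% to 95.1% with a separate week-5 variance. Mean half-widths were 4.54 against 5.56, 4.77 against 5.65 and 5.08 against 5.79, so 12% to 18% too narrow. With some week-5 scores missing (means 12 and 16), coverage was 88% to 92%, against 94% to 96% with an unstructured covariance. A wider grid (mean 10 to 25, SD 8 to 10, correlation 0.4 to 0.8) gave 88% to 94% with complete data.

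**Step 5, the primary contrast with complete data.** The group-by-time contrast depends only on within-participant differences. In one fitted data set its standard error was 2.618 under the random participant effect and 2.618 from the t-test on change scores. Simulated type I error was 4.9% to 5.1%.

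**Step 6, the primary contrast with missing week-5 scores.** The model slope of week 5 on baseline is 0.6 × V0 / ((V0 + V5)/2). This is 0.33, 0.38 and 0.44 for the three means, where the true slope is 0.6. The bias in an arm is (0.6 − model slope) × the gap in mean baseline between everyone in that arm and those still observed. A gap of 1 to 2 points gives from 0.16 × 1 = 0.16 to 0.27 × 2 = 0.54 points. Simulations and large-sample calculations with loss dependent on baseline gave about 0.2 to 0.9 points, depending on the pattern, against 0.2 or less with the unstructured covariance. For scale, the change SD is about 7.5; with 16 and 12 observed the standard error is 7.5 × √(1/16 + 1/12) = 2.9. Coverage of the change contrast stayed near nominal (93% to 94% in one set of runs).

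**Step 7, sensitivity.** If baseline is a separate assessment correlated 0.8 to 0.9 with the eligibility score, the standard error ratio is 0.89 to 0.95. If week-5 variance were half the baseline variance, the ratio would be √((1 + 2)/2) = 1.22 and coverage about 98%, so the intervals would be too wide.

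**The case against.** The strongest reply is that section 3.14 never states a constant residual. A random participant effect with a separate residual variance at each time fits the text, and with two assessments and a non-negative covariance it is the same model as the unstructured one. This is also a condensed article, and residual structure is often settled in the analysis plan. That stands against any claim that the text forces equal variances. It does not remove the point: the article names the fixed effects, the random effect, the estimation method and the type of test, and the ordinary reading of that list is a random-intercept model with one variance.

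Second, the outcomes in section 3.5 are changes, and no section names a week-5 group difference as a target. A reader might infer that the primary comparison is invalid. With complete data it is not, as step 5 shows.

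Third, a reader might infer that the full-scale trial will be undersized. Using the model SD for week-5 scores would understate N by 21% to 31%, since the squared SD ratio is 0.69 to 0.79. But neither section 3.7 nor 3.14 says that a model SD will be used, and raw week-5 or change SDs are free of the problem. This is a reason to name the SD, not a demonstrated error.

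Fourth, the loss patterns in step 6 are assumed. The article gives no attrition rate, and section 3.12 asks participants who discontinue to provide week-5 data.

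Fifth, section 3.9 mentions eligibility and baseline questionnaires, so baseline may be a separate measurement; the assessment schedule in Table 1 is not shown. K6 and GAD-7 have no entry cut-off, so direct truncation does not apply to them.

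**Conclusion.** The point holds as a cheap improvement to a stated model, not as a fault in the primary comparison. On its ordinary reading, section 3.14 gives CES-D one variance at two times at which the entry rule makes the variances likely to differ. If the eligibility score is the baseline and the assumed inputs are roughly right, 95% intervals for the week-5 difference cover about 88% to 92%. If week-5 loss depends on baseline, the change contrast can be off by roughly 0.2 to 0.9 points, a fraction of its standard error of about 3. The group-by-time contrast with complete data is unaffected.

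The direction requires week-5 variance above baseline variance. That is plausible after truncation at 16, but the article cannot show it. All sizes rest on an assumed SD, correlation and source mean.

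**What to change.** In section 3.14, keep the fixed effects and replace the random participant effect with an unstructured 2 x 2 within-participant covariance for baseline and week 5 (REPEATED with type UN in SPSS MIXED). Take the week-5 means, the week-5 difference and the change contrast, with their confidence intervals, from that model. State that the SD for Hedges g and for planning the full-scale trial comes from the observed week-5 or change scores, report the two separately, and do not use the pooled model variance.

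The cost is one or two sentences, one extra variance parameter, and somewhat wider week-5 intervals if the variances do differ as expected. The complete-data change contrast stays the same, and the model remains valid if the variances turn out equal or reversed.
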